## Abstract

**Background:**

Recent evidence shows that men and women have inadequate fertility knowledge which may negatively affect their childbearing decisions in future. Given the fact that decision making for fertility needs accurate information, targeted educational interventions especially through media are needed to improve knowledge regarding the best age of fertility, factors affecting fertility potential and fertility options available for sub-fertile couples. Aim of the study is to evaluate whether a fertility educational program can be effective in increasing fertility knowledge, childbearing intention and the planned pregnancy rate among couples referring to premarital counselling centers.

**Methods:**

This study is a parallel randomised clinical trial with pre-test/post-test design. We will recruit 1240 marrying couples referring for compulsory premarital counselling in public health centers through stratified sampling in five metropolitan cities of Iran. The intervention group will receive both the typical premarital counselling training and a fertility knowledge package containing verbal and virtual educational package at five time episodes (one verbal session and four virtual sessions) within 4 weeks. The primary outcomes are fertility knowledge, childbearing intention and the first planned pregnancy rate (positive pregnancy test) and the secondary outcomes include contraception method use, miscarriage and unplanned pregnancy. Participants will respond to a self-administered demographic/reproductive characteristics questionnaire, the Cardiff Fertility Knowledge Scale (CFKS) and the childbearing intention questionnaire.

Data will be collected through online questionnaires at baseline and 3, 12 and 18 months after the intervention. Data will be analyzed using Chi-square or Fisher-exact test for categorical variables, Independent sample t-test for normally distributed quantitative variables and Mann–Whitney U test for non-normally distributed quantitative variables. To compare the outcomes between the two groups over the time, repeated measures ANOVA will be used. We hypothesize that the positive impact of increasing the fertility knowledge is the reduced involuntarily childlessness.

**Discussion:**

The findings are proposed to inform government policies and public education strategies aiming at supporting childbearing among young couples who postpone their first pregnancy while they might not have any important social and economic obstacles.

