**Assessments**					
**Primary outcomes**					
fertility knowledge		**×**	**×**	**×**	**×**
childbearing intention		**×**	**×**	**×**	**×**
first planned pregnancy		**×**	**×**	**×**	**×**

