### Inclusion criteria

Marrying couples, having an Iranian nationality with minimum basic literacy, women aging from 18 to 35 years, men aging 18–45, with no previous marriage, referring to premarital counselling centers, and are about to live together in their new home (under one roof) within 1 month, will be included in the study. We will select a low-risk group of women for pregnancy according to women’s age.

An increasing number of women delay having children until after 35 years. Fertility clearly declines with advancing age, especially after the mid-30s and women are at greater risk of pregnancy complications. Therefore, we will include only women aged 18–35 as these women are making choices that may affect their intentions regarding the timing of childbearing (e.g., following education or career) and usually postpone childbearing decisions [32]. Semen parameters in men also decline detectably after 35 years of age but male fertility does not appear to be affected before 50 years old [33].

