### Exclusion criteria

Medical students or staff, participants who have any known chronic diseases and marrying couples who did not start living together will be excluded.

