#### Childbearing intention questionnaire

Parts of a questionnaire developed by Lampic et al. (2006) will be used in this study as the basis for the data collection regarding childbearing intentions that has satisfactory face validity and reliability and has previously been used by Lampic et al. (2006), Peterson et al. (2012) and Chan et al. (2014) in their studies of Swedish, American and Hong Kong university students [6, 16, 19]. The questionnaire contains five parts: (i) perceived knowledge of fertility issues (two items) asking about the perceived level of fertility-related knowledge; (ii) intention and potential obstacles of childbearing (seven items) including yes–no questions and open-response questions that aim to understand the ones’ intention to have children, as well as perceived obstacles; (iii) awareness of fertility issues (eight items) consisting of open-response items concerning changes in female fertility with age, and likelihood of pregnancy and infertility; (iv) importance of childbearing and intended behavior in the case of infertility (four items) containing four 0- to 10-point response scales assessing the perceived importance of childbearing and the preferred course of action in the case of infertility, and (v) conditions for parenthood (13 items) such as emotional readiness and financial stability that may be important in people’s decision to have children [16].

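### Childbearing intention and obstacles are recorded before the intervention, but the stated comparison of planned pregnancy does not use them; adjusting would gain precision, and the policy wording is narrower than the population enrolled

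*Protocol article*

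**What the plan says.** The aim in the Abstract (Background) is to test whether the programme is effective in "increasing fertility knowledge, childbearing intention and the planned pregnancy rate among couples referring to premarital counselling centers". Nothing in it is conditional on intention or obstacles.

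Inclusion criteria admit "women aging from 18 to 35 years, men aging 18–45, with no previous marriage, referring to premarital counselling centers", with further conditions on nationality, literacy and imminent cohabitation. The age range is explained partly by postponement: "we will include only women aged 18–35 as these women are making choices that may affect their intentions regarding the timing of childbearing". The exclusions are: "Medical students or staff, participants who have any known chronic diseases and marrying couples who did not start living together will be excluded". No criterion refers to a couple's own intention or obstacles.

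Table 1 lists "childbearing intention" and first planned pregnancy among the primary outcomes and marks both at allocation and at 3, 12 and 18 months. The Data collection section confirms a baseline questionnaire. The intention questionnaire includes a part on "intention and potential obstacles of childbearing (seven items"), answered by yes–no and open responses.

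For outcomes, the Statistical method section names repeated measures ANOVA between the two groups over time. It names no baseline covariate for planned pregnancy.

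On use of the results, the Abstract (Discussion) points to policies "supporting childbearing among young couples who postpone their first pregnancy while they might not have any important social and economic obstacles". The main Discussion ends on almost the same statement, with first birth in place of first pregnancy.

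**The concern.** Two things do not meet.

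First, for knowledge and intention a repeated measures analysis uses each outcome's own baseline. Planned pregnancy has no useful baseline of its own, because couples entering a first marriage and not yet living together can be expected to have nearly the same value. The natural baseline predictor is what they say before the intervention about wanting children and what stands in the way. That information is collected, but the stated comparison leaves it out. Randomisation protects the comparison from bias either way. What is lost is precision, on a primary outcome for which the sample size was not calculated.

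Second, the policy sentences name a subgroup (couples who postpone and may lack important obstacles) that neither eligibility nor the stated comparison identifies. An overall result would not by itself show an effect in that subgroup.

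**Working it through.** **The plan's own figure.** Inputs from the Sample size section: standardised difference d = 0.2, α = 0.05, power 90%, 15% loss. Sidedness is not stated; two-sided is assumed because it reproduces the figure (one-sided gives 429).

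- n per group = 2(1.96 + 1.2816)² / 0.2² = 526 by the normal formula. The t-test solution is 526.3, hence 527.
- 527 / (1 − 0.15) = 620 per group, 1240 in total.

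The 527 reproduces, but it was derived for knowledge and intention at 3 months. It serves below only as the number of couples analysed per group.

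**Gain from adjusting planned pregnancy.** The protocol gives no planned-pregnancy rate and no share of couples who intend an early pregnancy, so these are assumptions: a 50:50 split, 18-month planned pregnancy of 20% in non-intenders, and 50%, 60% or 70% in intenders.

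With two equal strata at rates a and b and mean p = (a + b)/2:

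- share of variance explained R² = ((a − b)/2)² / (p(1 − p))
- an adjusted analysis has about (1 − R²) times the variance of the unadjusted one, so it acts like 1/(1 − R²) times as many couples.

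| Intenders / others | p | R² | 1/(1 − R²) | 527 per group acts like |
|---|---|---|---|---|
| 50% / 20% | 0.35 | 0.0225/0.2275 = 9.9% | 1.11 | 585 |
| 60% / 20% | 0.40 | 0.0400/0.2400 = 16.7% | 1.20 | 632 |
| 70% / 20% | 0.45 | 0.0625/0.2475 = 25.3% | 1.34 | 705 |

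As confidence interval width, √(1 − R²) is 0.95, 0.91 and 0.86: intervals about 5%, 9% and 14% narrower. If the item used separates couples less well (for example, it asks about wanting children at all rather than soon), or the split is far from even, the gain is smaller. If intention does not predict planned pregnancy, it is nil.

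**Wording against population.**

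| Place | Population |
|---|---|
| Aim (Abstract, Background) | couples attending premarital counselling centres |
| Inclusion and exclusion criteria | restricted by age, nationality, literacy, first marriage, cohabitation, chronic disease and medical occupation; not by intention or obstacles |
| Statistical method | the two randomised groups |
| Discussion: adding the education to premarital courses | close to the population randomised |
| Abstract (Discussion) and last sentence of Discussion | couples who postpone and may have no important obstacles |

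Only the last row is narrower than what is enrolled and compared.

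**The case against.** **The design is coherent without this.** Aim, recruitment, eligibility and comparison all concern attenders at compulsory counselling, and the most concrete policy use, adding the education to those courses, needs the effect in attenders. The narrower sentences are hedged statements of intended use, not a hypothesis or a planned conclusion. This stands, and is why the whole enrolled population should remain the target of estimation.

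**Covariates are commonly left to the full protocol or SAP.** This also stands. The article's silence does not prove that no adjustment is planned, so the first part is an improvement to the stated comparison, not an error. If the SAP already names the covariate, only the wording remains.

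**The items may not code cleanly.** Part (ii) has open responses and is not shown to record intended timing or the importance of an obstacle. Only parts of the questionnaire will be used, and items may be revised. Both partners are recruited, and no rule covers disagreement between them. This stands against a defined target subgroup and limits the obstacle covariate. A simple intention covariate needs much less.

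**Stronger readings a reader might infer.** One is that the effect is diluted by couples who already plan a pregnancy. With a 10-point effect confined to the named group, control rates of 20–50% and 527 analysed per group, whole-sample power is 0.90–0.96 if every couple belongs to that group and 0.37–0.49 if half do. But the group's share, the rates and the confinement of the effect are all assumed. The package also covers the fertile window, lifestyle and earlier evaluation of infertility, which can matter to couples already trying. An average effect over attenders is the right answer to the stated aim.

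Another is that the policy claim goes untested. For adding the education to premarital courses, that is not so.

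A third is that eligibility admits all marrying couples. The criteria restrict in several ways, and the age range was chosen with postponement in mind.

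**Conclusion.** The point holds in a limited form. A prognostic measurement taken before the intervention is not used in the stated comparison of a primary outcome, and two policy sentences describe a narrower group than the one enrolled. The validity of the randomised comparison is not in doubt.

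Under the assumed rates the gain is equivalent to roughly 11–34% more couples. That range rests on the 50:50 split, on 20% in non-intenders and 50–70% in intenders, and on an item that separates the two. None of these comes from the documents. The documents do not support saying that the effect is diluted or that the policy use is untested.

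**What to change.** 1. In the Statistical method section, state that planned pregnancy will be compared between groups with baseline childbearing intention as a prespecified covariate, and baseline obstacles too if they can be coded reliably. Logistic regression with a standardised risk difference is one suitable form. Keep all enrolled couples as the target population.
2. Before unblinding, fix which part (ii) items are used, how open responses are coded, and how the two partners' answers form a couple-level value.
3. Label any treatment-by-baseline-intention or treatment-by-obstacle interaction as exploratory. A primary subgroup estimate is not recommended: under the illustrative assumptions above, power in the named group alone would be 0.64–0.76 if it were half the sample, and the items are not shown to define it.
4. Reword the Abstract (Discussion) and the last sentence of the Discussion to refer to eligible couples attending premarital counselling.

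The cost is protocol wording, a coding rule and one adjusted model. Eligibility, visits and questionnaires need not change. Couples with missing baseline answers will need a stated rule so that adjustment does not drop them.

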**Trial registration:**

This study was approved by Iranian Registry of Clinical Trials (IRCT), Number: IRCT20201005048925N1, Date of registration: 2020-10-12.

## Background

Recent evidence shows that men and women have inadequate fertility knowledge and awareness which may negatively affect their childbearing decisions in future [1–5]. For instance, some people underestimate the effect of age on fertility potential and overestimate the success rates of assisted reproduction [3, 6, 7]. They are unaware of consequences of postponed parenthood that may lead to a higher rate of infertility and maternal and child health risks with higher female and male age at fertility [8–10]. Therefore, there is a serious need for public education about age-related fertility declines and the availability, and limitations of assisted reproduction technologies [11, 12]. Hence, educational interventions are important to promote fertility knowledge and ensuring couples have a realistic perspective of fertility treatment [13].

Most of the people obtain fertility knowledge from the mass media or internet. Given the fact that decision making for fertility needs accurate information [5], targeted educational interventions specially through media are needed to improve knowledge regarding the best age of fertility, factors affecting fertility potential and fertility options available for sub-fertile couples [4, 14]. The majority of studies on fertility knowledge are cross-sectional and have studied women [14], university students [15–20] and/or people from high-income countries [4, 5, 10, 21] that making it difficult to generalize findings to new couples in developing countries.

In Iran, the fertility rates have dramatically declined over the past three decades, and the increased marriage age, delayed childbirth, significant rate of infertility (20.2) and a recent rise in voluntary childlessness require serious attention [22–24]. The total fertility rate in Iran has decreased in recent years and it fell into 2.2 in 2000,1.9 in 2006 and 1.7–1.8 in 2019, respectively [25]. Below replacement fertility has created some concerns among policymakers and scholars in Iran and has led to the announcement of pronatalist population policies in 2014 by the Supreme Leader [26]. Studies have also shown that fertility ideals are greater than fertility intention and behavior (well about 2 children) among the new couples in Tehran [27–29]. Therefore, any attempt to help couples to achieve their fertility ideals by removing obstacles of childbearing will be in line of new population policies of Iran.

Studies show that many social, economic and individual factors contribute to the lower fertility behavior among new generations. For instance, individual factors, women’s higher education and employment have been shown to be associated with lower fertility rate. Apart from these, poor fertility knowledge and misconceptions might be responsible for delay in childbearing among young couples [5, 30]. Evidence shows that people have little information about factors reducing their fertility chance [1, 6, 13]. A study in Iran also showed that 56% of Iranian couples did not have correct fertility information. Therefore, comprehensive educational interventions on fertility and factors reducing the fertility potential might be an effective strategy to help men and women to achieve their fertility goals before it gets late or they face infertility [31]. However, there is no evidence in Iran that how effective such interventions are in improving fertility knowledge and intention.

Fertility changes in Iran have been well monitored by demographers in recent years, and various individual and socio-economic factors have been considered to be responsible for fertility rate. Some new population policies have been introduced to encourage childbearing such as increased parental leave for a childbirth, while little has been done with regard to improvement of fertility knowledge. Considering the high rate of primary infertility (20.2%) [22], and a growing number of women electing to postpone childbearing in Iran [10, 23], it is important to assess fertility knowledge of new couples and also the effectiveness of an educational intervention based on fertility knowledge in their reproductive intention and behaviors. Evaluating the number of planned pregnancy (as a long term goal) in our study will demonstrate to what extent fertility knowledge can be translated to childbearing behavior.

## Methods/design

### Study aim

To evaluate the effectiveness of an educational intervention program on fertility knowledge, childbearing intention and planned pregnancy rate.

### Trial design

This study is a parallel randomised clinical trial with pre-test/post-test design among 1240 couples referring to premarital counselling centres. The flow diagram of the study design is reported in Table 1. We will also conduct a pilot survey on 30 couples to ensure the feasibility of the study, the appropriateness of the educational package and possible obstacles and problems and appropriateness of the study instrument.

**Table 1 Tab1:** Flow diagram of the study design

	STUDY PERIOD				
	Pre-intervention		Post- intervention		
**TIMEPOINT**	Enrolment	Allocation	3th month	12th month	18th month
**Enrolment**					
Eligibility screening	**×**				
Informed consent	**×**				
Randomization		**×**			
**Interventions**					
Intervention (fertility knowledge training)			**×**	**×**	**×**
Control (typical premarital counselling)			**×**	**×**	**×**
**Assessments**					
**Primary outcomes**					
fertility knowledge		**×**	**×**	**×**	**×**
childbearing intention		**×**	**×**	**×**	**×**
first planned pregnancy		**×**	**×**	**×**	**×**
**Secondary outcomes**					
contraception method use		**×**	**×**	**×**	**×**
miscarriage		**×**	**×**	**×**	**×**
unplanned pregnancy		**×**	**×**	**×**	**×**

### Setting and participants

This study will be conducted on couples referring for compulsory pre-marriage training in public health centers in five metropolitan cities of Iran with a diverse geographical distribution (Tehran, Mashhad, Ahvaz, Tabriz and Shiraz) to enhance the generalizability of the findings. We plan to recruit new couples (both men and women) referring for compulsory premarital counselling.

### Inclusion criteria

Marrying couples, having an Iranian nationality with minimum basic literacy, women aging from 18 to 35 years, men aging 18–45, with no previous marriage, referring to premarital counselling centers, and are about to live together in their new home (under one roof) within 1 month, will be included in the study. We will select a low-risk group of women for pregnancy according to women’s age.

An increasing number of women delay having children until after 35 years. Fertility clearly declines with advancing age, especially after the mid-30s and women are at greater risk of pregnancy complications. Therefore, we will include only women aged 18–35 as these women are making choices that may affect their intentions regarding the timing of childbearing (e.g., following education or career) and usually postpone childbearing decisions [32]. Semen parameters in men also decline detectably after 35 years of age but male fertility does not appear to be affected before 50 years old [33].

### Exclusion criteria

Medical students or staff, participants who have any known chronic diseases and marrying couples who did not start living together will be excluded.

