### Interventions

The intervention group will receive both the typical premarital counselling and a fertility knowledge training containing verbal and virtual educational program at five time episodes (one verbal session and four virtual sessions) in a package. We will implement the educational programs during 4 weeks. The intervention includes a 30-min lecture, documentary videos, text messages and short films. The control group will receive only typical premarital counselling. The content of educational or counselling program will be based on the most updated literature on fertility knowledge.

The educational program was developed based on new guidelines of American Society for Reproductive Medicine (ASRM), European Society of Human Reproduction and Embryology (ESHRE) and Iran’s Ministry of Health and Medical Education (MOHME).

The fertility knowledge package will consist of information on fertility rates, infertility rates, risks of delay in childbearing, safe waiting period for parenting, Impact of age on female fertility, limited fertility period for women, fertility window and how to optimize fertility, impact of weight and lifestyle on fertility, definition of infertility, infertility risk factors, impact of sexually transmitted diseases (STDs) on fertility, the need for earlier evaluation and treatment of infertility, success rate and financial costs of infertility treatments, assisted conception and fertility preservation. In order to incorporate multidisciplinary views in this study, specialists from different relevant disciplines will be invited to provide their views on different stages of the study including the suitability of the educational content. A group of experts composed of midwife, reproductive health professional, gynecologist (infertility fellowship), medical sociologist, health psychologist and health education will evaluate and confirm the scientific validity of the intervention package. The content of educational program will be also assessed in the pilot phase.

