### Data collection

Data will be collected by questionnaires at baseline and 3, 12 and 18 months after the intervention in each selected city (Table 1). The post-test questionnaires will be completed by the participants through online forms. The participants’ phone number, email address and social network’s ID (WhatsApp) will be asked in order to send the post-test questionnaire links and some virtual educational materials.

In each city, two research collaborators will cooperate with the principal investigator. They will be introduced by the Ministry of Health and Medical Education, associated office for premarital counselling courses in all provinces. We will have a training session for these research staff and they will be justified about the study aims and procedure of data collection as well as educational intervention. They need to be in close contract with the principal investigator.

To minimize loss to follow up, we will provide an incentive to the eligible participants (A gift voucher for free sexual and reproductive health counselling) on the completion of the survey which may increase response rates. Four reminder emails or text messages will send out to non-respondents at one, two, three, and 4 weeks; a fifth telephone reminder was also undertaken.

Since a recent study in Iran showed an average interval between marriage and first pregnancy as about 15.4 ± 0.2 months in Iran [24], we are planning to follow the participants for occurrence of planned pregnancy about 18 months after the intervention.

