### Blinding

Given the nature of the intervention, it is not possible to blind participants to researchers involved in providing the intervention and data collection. However, allocation to intervention or control groups will be blinded for researchers in the data set available during the data analysis. To avoid the potential contamination between two groups, we will provide the educational intervention after the typical premarital counselling.

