### Ethical considerations

The ethical approval of the research project was obtained from the ethics committee of National Institute for Medical Research Development (NIMAD) (IR.NIMAD.REC.1399.123). Eligible couples will be invited for an additional counselling by a health provider to ensure that they are entirely informed on the nature of the research by means of oral and written information. All the participants who agree to participate in the study, will sign a written informed consent before the randomization. All participants have the right to withdraw from the study anytime and for any reasons. The educational package will be provided to the control group as well upon their request at the end of the study. To protect against loss of confidentiality, data sheets will be stored on a password-protected computer, which can be accessed only by the members of the research team. Information on participants will be sent to the PI only as de-identified, aggregate data.

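### The rule that excludes couples who did not start living together most naturally acts after randomisation, and could bias the planned-pregnancy comparison if it operates differently in the two arms

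*Protocol article*

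**What the plan says.** All statements are from the protocol article.

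- **Setting and participants:** "We plan to recruit new couples (both men and women) referring for compulsory premarital counselling".
- **Inclusion criteria:** eligible couples "are about to live together in their new home (under one roof) within 1 month, will be included in the study". At entry, moving in together is still to come.
- **Exclusion criteria:** "marrying couples who did not start living together will be excluded". The other two items in that sentence, medical background and chronic disease, are baseline characteristics.
- **Ethical considerations:** participants "will sign a written informed consent before the randomization". No further condition is set between consent and allocation.
- **Blinding:** "we will provide the educational intervention after the typical premarital counselling". The same section says that "it is not possible to blind participants to researchers involved in providing the intervention and data collection"; only the data set used for analysis is masked.
- **Interventions:** "We will implement the educational programs during 4 weeks".
- **Data collection:** "Data will be collected by questionnaires at baseline and 3, 12 and 18 months after the intervention".
- **Sample size and Randomization:** 620 couples per group with 15% loss to follow-up as the only attrition allowed for, and block lists for exactly 1240 couples.

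**The concern.** A couple's failure to move in can be established only once the month allowed for it has passed. If the couple has been randomised by then, excluding it selects the analysed groups on a post-allocation event, and randomisation no longer guarantees that those groups are comparable.

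This matters most for planned pregnancy. Couples who never set up home together can be expected to have few planned pregnancies, so the number removed from each arm feeds directly into the observed rate. The package also covers the risks of delaying childbearing and runs in about the same month in which couples are due to move in, and participants know their arm. Either the event itself or the reporting of it could therefore differ between arms.

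A second, smaller cost is power, because the sample size has no separate allowance for such removals.

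**Working it through.** **Step 1. When can the rule act?** Entry requires cohabitation to lie ahead, by up to 1 month. Consent and randomisation follow with no waiting period stated, and Table 1 places randomisation before the intervention. The package then runs for 4 weeks. There are two ways to read the exclusion:

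- *At screening:* the clause would exclude couples not yet living together, which are the couples that the Inclusion criteria admit. The two sections would contradict each other.
- *After the month has passed:* the sections agree, but the rule acts during or after the intervention, on randomised couples.

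The second reading is the more natural. It remains an inference, since no sentence dates randomisation against cohabitation.

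**Step 2. Reproduce the plan's sample size.** Inputs from the Sample size section: d = 0.2, alpha 0.05 (taken as two-sided), power 90%, loss 15%.

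- n per group = 2(1.960 + 1.282)²/0.2² gives 526; the t-based solution is 526.33, rounded up to 527.
- 527/0.85 = 620 per group.
- Block lists: 110 × 4 = 440 for Tehran, 50 × 4 = 200 for each of four other cities; 440 + 4 × 200 = 1240.

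The stated figures reproduce. They are reached without the design effect of 1.5 named in the same section, which is a separate matter and is left aside here.

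**Step 3. Power if couples are removed beyond the 15%.** The fraction removed, q, is assumed. Evaluable couples per group m = 620 × 0.85 × (1 − q); power = Φ(0.2 × √(m/2) − 1.96).

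| q | m | power |
|---|---|---|
| 0% | 527 | 90.1% |
| 2% | 516 | 89.5% |
| 5% | 501 | 88.6% |
| 10% | 474 | 86.9% |
| 15% | 448 | 84.9% |
| 20% | 422 | 82.7% |

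If these couples fall within the 15%, there is no loss beyond what was planned.

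**Step 4. Bias in planned pregnancy.** Every rate here is assumed; the article gives none.

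*(a) No true difference, unequal removal.* Let p be the overall rate in both arms and p₀ the rate among removed couples. The retained rate is (p − q·p₀)/(1 − q).

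| p | p₀ | removed, arm 1 vs arm 2 | retained rates | spurious difference |
|---|---|---|---|---|
| 30% | 2% | 5% vs 5% | 31.5% vs 31.5% | 0 |
| 30% | 2% | 5% vs 10% | 31.5% vs 33.1% | 1.6 points |
| 30% | 2% | 5% vs 15% | 31.5% vs 34.9% | 3.5 points |
| 40% | 5% | 5% vs 10% | 41.8% vs 43.9% | 2.1 points |
| 40% | 5% | 5% vs 15% | 41.8% vs 46.2% | 4.3 points |

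*(b) A real difference hidden.* Suppose 60% of cohabiting couples in each arm have a planned pregnancy, non-cohabiting couples have none, and 8% vs 4% fail to move in. The analysed comparison is 60% vs 60%. As randomised it is 0.60 × 0.92 = 55.2% vs 0.60 × 0.96 = 57.6%, a difference of 2.4 points.

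**Step 5. Scores.** If removed couples differ from retained ones by D standard deviations, the bias is D × (difference in fractions removed). With 5% vs 15% and D = 0.5 to 1.0, this is 0.05 to 0.10 SD, or 25% to 50% of d = 0.2. Nothing in the article shows that knowledge or intention depends on cohabitation to that degree, so this is only an outer illustration.

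**The case against.** The strongest reply is that the clause sits in a short eligibility list beside two baseline criteria, and Table 1 puts eligibility screening before allocation. It may be meant only as the mirror of the inclusion rule: no imminent plan to live together, no entry. The past tense is weak evidence, because the article's tenses are loose elsewhere; the telephone reminder in Data collection is also put in the past. No sentence says that a randomised couple will be dropped from follow-up or analysis. This stands as far as it goes: the timing is inferred. But if the mirror reading is intended, the clause does not say so, and taken literally at screening it conflicts with the inclusion rule. Either way the text needs changing.

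It is also fair that unequal removal is speculative. Couples enter already planning to move in, and no listed topic of the package concerns moving in. With equal fractions of similar couples, bias is nil. This stands and limits the point to a possible bias.

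An analysis plan that is not shown may define the analysis sets. The absence of a named intention-to-treat population is therefore not the point. The point is a stated exclusion rule, which a plan restricted to eligible couples would inherit.

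Three stronger readings are tempting, and the documents support none of them:

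- *That the randomised comparison is certainly lost.* The timing is inferred, and harm requires a difference between arms.
- *That unblinded staff will decide who is removed.* No section says who records cohabitation, and post-test questionnaires are completed online by participants.
- *That all three primary outcomes are distorted.* A clear link exists only for planned pregnancy.

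**Conclusion.** The point holds in a limited form. As written, the exclusion most naturally removes randomised couples on a post-allocation event in an open trial, and the planned-pregnancy comparison is the one exposed. Whether bias arises, in which direction and how large cannot be derived from the article. The illustrated shifts of about 1.6 to 4.3 percentage points rest wholly on assumed pregnancy rates and assumed unequal removal of 5% against 10% or 15%.

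Without such imbalance, the cost is a small loss of power: from 90% to about 89% with 5% removed and about 87% with 10%, on the further assumption that these couples come on top of the 15% allowance. Those power figures concern the d = 0.2 calculation for knowledge and intention at 3 months, not planned pregnancy. The effect on the two scores themselves is uncertain.

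The correction is cheap and is best made before recruitment, because couples dropped from follow-up cannot be recovered at analysis.

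**What to change.** - Keep the declared plan to live together within 1 month as an entry criterion, assessed before randomisation.
- Delete the clause on couples who did not start living together as a ground for removal after randomisation.
- State that every randomised couple is followed at 3, 12 and 18 months and analysed in its allocated group.
- Report the number of couples who did not start living together, by arm.
- Keep the analysis restricted to cohabiting couples as a labelled sensitivity analysis.

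The cost is a change of wording and continued online follow-up of what is likely to be a small number of couples, through forms already planned. The statistical downside is a slight dilution of the planned-pregnancy effect, since couples who do not cohabit stay in the denominator.

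Randomising only after cohabitation is confirmed would also remove the problem, but the passages on the timing of the intervention relative to counselling would then have to be reworked. That makes it the more disruptive option.
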